### 5.3 Other Outcomes of Interest

n.a.

### 5.4 Safety Outcomes

The individual components of the primary outcome are defined as safety outcomes. The occurrence of an adrenal crisis is of particular relevance due to its obvious danger for the patient. At the same time, papers reporting unequivocal, non-circumstantial evidence of true glucocorticoid-responsive shock in **secondary** (glucocorticoid-induced) adrenal insufficiency are exceedingly rare and date back well into the last century. Because it is not realistic to choose this event as single endpoint, it was defined as one component of the composite primary outcome.

Judging from the literature, it is likely that the imminent danger of adrenal crisis in secondary adrenal insufficiency is overestimated quantitatively. This is supported by our own data from the REDUCE trial. As in the REDUCE trial, patients in this trial will receive a written instruction on signs and symptoms of hypocortisolism and will be provided with five 10 mg tablets of prednisone to cover increased needs for glucocorticoids in emergency situations. This approach has proven effective in the REDUCE trial, where approximately one third of the study patients were discharged from the hospital with biochemically suppressed adrenal glands, but not a single critical incident was provoked by glucocorticoid deficiency during 6 months of follow-up.

---

## 6. STUDY DESIGN

### 6.1 General study design and justification of design

This is an investigator-initiated, placebo-controlled, multicenter noninferiority trial, comparing rapid termination of systemic glucocorticoid treatment with a tapering regime over 4 weeks.

**Rationale.** To date, there are no published RCTs comparing glucocorticoid tapering with rapid stopping, with regard to hazards resulting from adrenal failure or to disease relapse. Data from trials comparing different tapering schemes in patients treated for inflammatory or autoimmune disorders are scarce and inconclusive. A systematic review found “insufficient evidence about the efficacy and safety of different glucocorticoid withdrawal regimens” and demonstrated “a research gap of high quality randomized trials in a wide range of chronic disorders.” The review evaluated 9 trials (Crohn’s disease: 1; graft versus host disease: 1; bronchial asthma: 5; COPD: 2), 7 of which included less than 50 patients. Our own literature search in PubMed has produced no systematic reviews or meta-analyses published after the report by Richter et al. Given the very small scientific evidence base for the common clinical situation of glucocorticoid withdrawal and the potential for serious untoward effects of these drugs, a noninferiority trial should be conducted to test the hypothesis that an inferior outcome will not result from abrupt glucocorticoid stop even in the presence of biochemically suppressed adrenal glands. From our previous own data, we have no evidence that abrupt withdrawal will endanger patients even in the presence of biochemical adrenal insufficiency. However, it is important to note that potential hazards of adrenal insufficiency will not be underestimated in our trial. Treating physicians will be informed about their patients’ participation in the trial, and patients will be instructed on when and how to use rescue glucocorticoids. These safety measures were also taken in the “REDUCE” trial (cf. paragraph 5.4. above).

**Glucocorticoid therapy prior to enrolment.** The issue of time and duration of glucocorticoid treatment as well as the daily dosage upon enrolment is critical and has been extensively discussed among the planning committee and the collaborating researchers. In order to maximize the proportion of patients with adrenal suppression, an intuitive approach would be to include participants who are on a current dose as high as possible and have received treatment for as long as possible. However, our own data and published evidence suggest that the cumulative dose and duration of treatment does not allow to predict adrenal suppression, although the contrary observation has also been reported. Also, the abrupt stop from a relatively high daily dose (e.g. 30 or 40 mg prednisone-equivalent), administered over a prolonged period (weeks to months) might increase the event rate due to frequent symptoms because of glucocorticoid resistance, even if the HPA axis is recovering. In many inflammatory and autoimmune disorders, glucocorticoids are tapered to prevent a relapse, although tapering schemes are not standardized in rheumatoid arthritis, polymyalgia rheumatica, brain edema due to tumor metastases, sarcoidosis, asthma, and other diseases. Thus, at the time of inclusion, patients must be on a dose low enough to permit an abrupt stop, as judged by the treating physician, but high enough to still suppress the HPA axis. Based on these considerations, the planning committee settled on a treatment duration of  $\geq 28$  days, and a minimal cumulative dose of 420 mg. The minimum average daily dose must be at least 7.5 mg prednisone-equivalent, and patients must still be on a daily dose of  $\geq 7.5$  mg prednisone-equivalent as inclusion criterion. We expect many patients with eligible diseases to have considerably higher cumulative exposure, e.g. those with sarcoidosis, inflammatory bowel disease, polymyalgia rheumatica, rheumatoid arthritis, autoimmune hemolytic anemia, and other autoimmune disorders.

**Patients and Procedures.** In total, 573 patients will be enrolled. Patients will be randomly assigned in a 1:1 ratio to either prednisone in decreasing doses over 4 weeks or placebo using a centralized secured study website, programmed by the CTU Basel, to ensure allocation concealment. Patients, treating physicians, and study personnel will be blinded to treatment allocation to either prednisone or matching placebo. At inclusion, we will perform a 250 mcg ACTH (Synacthen®) stimulation test  $\geq 24$  hrs. after the last glucocorticoid dose to avoid interaction of prednisone with endogenous cortisol. We chose this test because, unlike the low-dose (1 mcg) test, it is widely available and can be performed by personnel of various disciplines. The results of the test will be blinded to treating physicians and investigators, and its value to predict clinical outcome will only be assessed after completion of the trial. As a safety measure, all patients will be instructed about stress coverage as well as signs and symptoms of hypocortisolism and will be provided with emergency medication, as described above (paragraph 5.4). Treating physicians, including those in primary care, will be informed about their patients’ participation in the trial to increase awareness of potentially occurring hypoadrenergic symptoms. Patients will be randomized to the standard (tapering) or the experimental (matching placebo) arm. The rate at which glucocorticoid should be tapered in the standard arm has been extensively discussed among collaborators and other experts from endocrinology and specialties treating prospective study patients (general internists, gastroenterologists, neurologists, pulmonologists). Although ideally chosen for the standard arm in a noninferiority trial, there is no published standard, “best-of-care” glucocorticoid tapering scheme, but a large variety of expert opinions. Also, there are no controlled data indicating the superiority, with respect to clinical outcome of the underlying disease, of one particular tapering scheme over another, or of tapering versus abrupt stopping. Thus, for many inflammatory and autoimmune disorders, there are no specific guidelines as to the tapering regimens. If there are recommendations to taper to a daily dose below 7.5 mg of prednisone equivalent, e.g. in giant cell arteritis, patients with the respective disorder are not eligible for the study. After careful reflection of all these aspects, the planning committee has settled on the regimen depicted in the figure below. Follow-up will be for six months. We do not think that a longer follow-up period is helpful because proportions of patients with suppressed adrenals will be low at six months (2% in our previous REDUCE trial), the necessary sample size does not change appreciably, and loss to follow-up would likely increase.

In order to improve adherence to the study and ensure feasibility, follow-up visits in most study centers will be by telephone only. Visits will be performed early after stopping glucocorticoids in both arms (i.e. at days 7 and 35) to ensure safety; the other two visits will be on days 90 and 180. In a subset of 180 patients, we will also perform clinical visits on days 7 and 35.

Figure: Study Algorithm

[figure not shown]

**Days 7 and 35 :** Due to limited resources, clinical visits will be performed only in a subgroup of 180 patients living in vicinity to their respective trial site, including examination of vital signs and 250 mcg synacthen test.

## 6.2 Methods of minimising bias

### 6.2.1 Randomization

The CTU Basel will generate the randomization list, which will be concealed to all study personnel. Patients will be randomly assigned in a 1:1 ratio, stratified according to trial site, age group, and daily prednisone dose at inclusion, to either prednisone in decreasing doses over 4 weeks or placebo. The randomisation procedure will be implemented into the electronic data capture software SecuTrial®. It will include a standard minimisation algorithm which will ensure that the treatment groups are balanced within each stratum. To avoid predictable alternation of treatment allocation, and thus potential loss of allocation concealment, patients will be allocated with a probability of 70 percent to the treatment group that would minimise the difference between the groups within the patient's stratum. Study medication will be pre-packed in glass vials; vial numbers will correspond to the pertinent number on the randomization list.

---

### **6.2.2 Blinding procedures**

Blinding of trial participants, treating physicians, study doctors, study nurses, outcome assessors and data analysts will be ensured by using identical-looking placebo, packaged in identical vials as the prednisone verum. Vials will be labeled with "Prednisone or Placebo" in an identical fashion.

### **6.2.3 Other methods of minimizing bias**

n.a.

## **6.3 Unblinding Procedures (Code break)**

Unblinding is permissible and procedures for revealing a participant's allocated intervention will be allowed if knowledge of the patient's study medication is essential for further treatment. Unblinding may be performed by the local investigator at any time to ensure patient safety and is executed via the online database tool (SecuTrial). The members of the DSMB have access to the randomization list and have the competence to terminate the trial prematurely.

## **6.4. End of the trial**

The trial end with the last visit of the last patient has been completed (day 180 of the follow-up). If a SAE is still ongoing at this time point, it will be followed up until its resolution.

---

## 7. STUDY POPULATION

### 7.1 Eligibility criteria

Both in- and outpatients are eligible. Outpatient participants may be followed in specialty clinics or by general practitioners in their practice. Inpatient participants may be hospitalized on organ-specific or on general internal medicine wards of the participating trial sites (see p. 12, paragraph 1.2).

**Participants fulfilling all of the following inclusion criteria are eligible for the study:**

- Informed Consent as documented by signature (Appendix Informed Consent Form)
- Age  $\geq 18$  years
- Daily glucocorticoid dose  $\geq 7.5$  mg prednisone-equivalent at the time of inclusion
- Therapy over  $\geq 28$  days,  $\geq 7.5$  mg average daily dose, cumulative glucocorticoid dose  $\geq 420$  mg prednisone-equivalent prior to inclusion
- Tapering not or no longer mandatory to treat underlying disease

**The presence of any one of the following exclusion criteria will lead to exclusion of the participant:**

- Primary adrenal failure
- Treatment with systemic depot glucocorticoids (e.g. intramuscular, epidural)
- Incapability to administer glucocorticoid cover treatment in situations of stress
- Inability or unwillingness to provide informed consent
- Women who are pregnant or breast feeding,
- Intention to become pregnant during the course of the study,
- Lack of safe contraception, defined as: Female participants of childbearing potential, not using and not willing to continue using a highly effective method of contraception, as defined by the Clinical Trial Facilitation Group (CTFG) for the entire study duration, i.e. hormonal contraception with inhibition of ovulation, intrauterine device, intrauterine hormone-releasing system, bilateral tubal occlusion.
- Known or suspected non-compliance
- Inability to follow the procedures of the study, e.g. due to language problems, psychological disorders, dementia, etc. of the participant,
- Participation in another study with investigational drug within the 30 days preceding and during the present study,
- Previous enrolment into the current study,
- Enrolment of the investigator, his/her family members, employees and other dependent persons
- Untreated hereditary galactose intolerance or lactase deficiency or glucose-galactose malabsorption

If the goals for recruitment are not met, an effort will be made to open additional trial sites.

### 7.2 Recruitment and screening

Eligible patients are screened for by local investigator or a member of the study team at each center. Participating physicians in private practices will evaluate patients for potential screening and suggest screening for potential participation at one of the trial sites in the Basel area (University Hospital Basel, Kantonsspital Baselland site Liestal, whichever is most suitable for the patient). Screening is based on analysis of prescribed systemic glucocorticoids, as listed in the patients' charts, and on consultation with the treating physician; this may be done by a study nurse or a study physician. Electronic or paper hospital charts (depending on the prevailing method used by the participating center) will be checked daily. Patients willing to participate will receive written and oral instruction on the trial and give written informed consent.

Patients will not be offered compensation for their participation, except for a refund for their public transportation fees.

### 7.3 Assignment to study groups

Patients will be randomized by local members of the study teams (physician or trained study nurse) in a 1:1 ratio using an online randomization tool programmed by the CTU Basel which will be accessible over a secured website. The generated randomization code will correspond to the batch number of the pre-packed study medication containing verum or placebo.

### 7.4 Criteria for withdrawal / discontinuation of participants

The decision about all pharmacological therapy, including unplanned glucocorticoid treatment, will entirely rest with the treating physician, not the study team. Unplanned (rescue) glucocorticoid treatment may also be initiated by the

---

participating patient in case of symptoms of glucocorticoid deficiency (see also section 8.6. below). The trial compares two regimens with an approved drug in registered indications, thus there are no withdrawal criteria concerning drug-related aspects. Rather, unplanned (rescue) glucocorticoid treatment will be assessed as component of the primary outcome.

Reasons for exclusion of a patient include withdrawal of informed consent or non-compliance. Study subjects may choose to withdraw from the trial, both during the treatment or follow-up phase, without justification. Substitute patients for drop-outs will be recruited. See also point 9.2.5 below.

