### **8.4 Compliance with study intervention**

Patients will be asked to fill out a medication diary over the 4-week treatment phase. Adherence to study medication will be ascertained during the follow-up telephone visits at days 7 and 35 when patients will be asked to count tablets remaining in the vials ("pill count"). All patients will be asked to send back the spare tablets at the end of the treatment phase or return them at the visit on day 35, if this is a hospital visit. A sensitivity analysis will be performed to determine a compliance cutoff, i.e. a critical percentage of ingested study medication, below which an association with the outcome is visible.

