### **8.5 Data Collection and Follow-up for withdrawn participants**

Patients who choose to withdraw from the study during the treatment intervention will be considered as drop-outs. Patients who choose to withdraw from the study during the follow-up period (i.e. refuse to participate in the telephone interviews on days 35, 90, and 180 or to come to the outpatient visit on day 35, if applicable) will be asked for permission to contact their treating physician for inquiry of the 1° outcome and to use their data collected so far. This will prevent their drop-out. If patients do not permit the inquiry of the 1° outcome, their data will be considered right-censored from the last documented contact onward.

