### 11.2 Determination of Sample Size

To assess the primary outcome measure, a Cox proportional hazards regression model will be fitted to the data. Non-inferiority will be concluded if the two-sided 95% confidence interval of the hazard ratio between the experimental and the control arm lies entirely below the critical hazard ratio defined as

$$HR = \frac{\lambda_e}{\lambda_c} = \frac{\frac{-\log(\pi_{et})}{t}}{\frac{-\log(\pi_{ct})}{t}} = \frac{\log(\pi_{et})}{\log(\pi_{ct})} = \frac{\log(\pi_{ct} - m)}{\log(\pi_{ct})}$$

where  $\lambda_e$  and  $\lambda_c$  are the hazard rates in the experimental and control arms,  $t$  is a fixed point of time,  $\pi_{et}$  and  $\pi_{ct}$  are the proportions of event-free patients at time  $t$ , and  $m$  is the non-inferiority margin expressed as the additional proportion of patients having had an event in the experimental arm, assuming that the occurrence of events follows an exponential distribution. Noninferiority will be concluded if the upper limit of the two-sided 95% confidence interval of the hazard ratio lies below the critical hazard ratio.

For the sample size estimation, the following assumptions were made:

- Patients are randomized to the control and experimental arms in a 1:1 ratio.
- After inclusion, all patients are followed for 6 months. Patients without an event within 6 months are considered right-censored and are not followed any further even though the trial might be ongoing.
- 10% of patients drop out within the 6 months follow-up period. The drop-out events are distributed uniformly over this period.
- The event rate within the 6 months follow-up period, i.e., the proportion of patients with an event, is 40%, both for the control and the experimental arms. We estimated this overall figure based on expected relapse rates for the various eligible diseases, as indicated by clinical experts and published data, e.g. in COPD or inflammatory bowel disease. Our estimation is conservative since the other components of the combined primary outcome will contribute to the event rate.
- The survival curves in the control and experimental arms follow the same exponential distribution. The rate parameter of the exponential distribution is chosen so that the corresponding cumulative distribution function value at 6 months equals the assumed event rate.

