- The non-inferiority margin is defined as an absolute increase of the event rate by 13% over 6 months. We used a modified Delphi approach to determine this margin. 10 experienced clinicians board-certified in internal medicine and/or rheumatology, gastroenterology, and endocrinology were individually asked to define the maximum increase in outcome events they would accept for the benefit of rapid glucocorticoid stop and gain of high-quality scientific data in the area of steroid withdrawal. Assuming an event rate of 40% in the standard treatment arm, the mean tolerable increase under experimental treatment was 13.6% (range, 5 to 20%; median, 13%).
- The significance level is 5%.

For each combination of the noninferiority margins 7.5%, 7.6%, ..., 17.5%, and the sample sizes  $n = 200, 210, \dots, 1200, 999$  individual data sets were simulated based on the above assumptions. A Cox proportional hazards regression model was fitted to each data set, and the hazard ratios for the experimental vs. the control arm with the associated 95% confidence interval were estimated. Noninferiority was concluded if the upper limit of the two-sided 95% confidence interval of the hazard ratio was below the critical hazard ratio (see above equation). The power was estimated as the proportion of positive conclusions divided by the total number of the 999 iterations per parameter combination. To achieve a power of 80%, 573 patients (95% CI, 565 to 580) need to be included, assuming an event rate of 40% over the 6 months follow-up period and setting the non-inferiority margin to 13% (Figure). The critical hazard ratio for this noninferiority scenario is 1.478.

The sample size of  $n=573$  is a conservative estimation, since the assumed drop-out rate of 10% is relatively high.

[figure not shown]

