#### 11.4.1 Datasets to be analysed, analysis populations

The full analysis set (FAS) consists of all patients who are randomised.

The intention-to-treat (ITT) set is a subset of the FAS that consists of all patients for whom the primary endpoint is available. Patients are assigned to the treatment arm they are randomised to.

The per protocol (PP) set includes the same patients as the ITT set, but patients are assigned to the treatment arm that corresponds to the actually obtained treatment.

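### Section 7.4 allows a randomised patient to be excluded for undefined non-compliance, and no section clearly requires the primary outcome to be obtained afterwards if no event was recorded before the exclusion.

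*Protocol*

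**What the plan says.** Section 7.4, on withdrawal and discontinuation, reads: "Reasons for exclusion of a patient include withdrawal of informed consent or non-compliance". This applies after enrolment; known or suspected non-compliance at screening is a separate exclusion criterion in section 7.1. Section 7.4 gives no definition or threshold and does not say who decides. It then deals separately with subjects who choose to withdraw, and it refers to section 9.2.5.

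Four places bear on what happens to the outcome afterwards:

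- Sections 8.5 and 9.2.5 (identical text) describe "Patients who choose to withdraw from the study during the follow-up period". They are asked for permission to obtain the primary outcome from their physician and are otherwise censored at last contact. Patients who withdraw during the treatment phase are simply counted as drop-outs.
- Section 10.1.3, on follow-up of serious adverse events, has the physician contacted for the primary outcome when a participant is lost to follow-up without having asked to leave.
- Section 11.5 says that events can be inquired from treating physicians where necessary.
- Section 11.4.1 defines the ITT set as "a subset of the FAS that consists of all patients for whom the primary endpoint is available". The PP set holds the same patients, and section 11.4.2 runs the primary analysis on it. No analysis is assigned to the full analysis set.

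On compliance, section 8.4 plans: "A sensitivity analysis will be performed to determine a compliance cutoff, i.e. a critical percentage of ingested study medication". The aim is to find the level of intake under which poor compliance begins to relate to outcome.

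**The concern.** The rule turns a fact about tablet-taking or attendance into a reason for ending participation, and no passage clearly asks for the outcome of a patient who leaves in this way. That patient has consented and has not withdrawn, so the protocol itself creates the missing outcome. A later analysis plan cannot recover data that were never collected.

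The loss may be informative. Adherence is first checked at day 7, when one arm takes placebo and the other takes prednisone. If feeling unwell leads some patients to stop their tablets, this could be more frequent in the abrupt-stop arm, and such patients could be at higher risk of a later event. Losing them before the event is recorded pulls the hazard ratio towards 1. In a non-inferiority trial that is the direction that favours the claim, so the chance of accepting a truly inferior regimen would rise above its nominal level.

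The rule also works against section 8.4, whose planned analysis needs outcomes in the patients that section 7.4 allows to be excluded.

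**Working it through.** **Inputs from section 11.2.** The event rate is 40% over 6 months and allocation is 1:1. The margin: "The non-inferiority margin is defined as an absolute increase of the event rate by 13% over 6 months". The sample size: "To achieve a power of 80%, 573 patients (95% CI, 565 to 580) need to be included". Non-inferiority is concluded if the "upper limit of the two-sided 95% confidence interval of the hazard ratio lies below the critical hazard ratio", which is a one-sided error of 2.5%. Drop-out is 10%, uniform over 6 months.

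**The plan's own figures.** Critical HR = ln(0.60 − 0.13)/ln(0.60) = ln(0.47)/ln(0.60) = 1.478, as stated. Schoenfeld's formula for this HR, two-sided 5% and 80% power, gives 206 events; 206/(0.40 × 0.90) = 572.2, hence 573. The sample size is not in question.

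**Assumptions that the protocol does not supply.** The true rates lie exactly at the margin (53% v 40%). A share k of the abrupt-stop arm, with event risk r, is removed before any event is recorded. Nobody is removed from the control arm.

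**Formulas.** The arm has 573/2 = 286.5 patients.

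- Remaining rate: p = (0.53 − k·r)/(1 − k)
- Observed HR = ln(1 − p)/ln(0.60)
- SE = 2/√D, where D is the total number of events reduced by 5% for drop-out
- Error = Φ[(ln 1.478 − ln HR)/SE − 1.96]

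**k = 5%, r = 0.8** (14.3 patients, 11.5 events removed)

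- p = (0.53 − 0.04)/0.95 = 0.516
- HR = 0.7252/0.5108 = 1.42
- D = 0.95 × (140.4 + 114.6) = 242.2, so SE = 0.1285
- Error = Φ(−1.65) = 5.0%

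**k = 10%, r = 0.8** (28.7 patients, 22.9 events removed)

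- p = (0.53 − 0.08)/0.90 = 0.50
- HR = 0.6931/0.5108 = 1.36
- D = 0.95 × (128.9 + 114.6) = 231.3, so SE = 0.1315
- Error = Φ(−1.31) = 9.5%

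**Range over the assumptions, same formulas**

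| Share of abrupt-stop arm removed | r = 0.7 | r = 0.8 | r = 0.9 |
|---|---|---|---|
| 0% | 2.5% | 2.5% | 2.5% |
| 2% (about 6 patients) | 3.0% | 3.3% | 3.7% |
| 5% (about 14) | 3.9% | 5.0% | 6.3% |
| 10% (about 29) | 6.1% | 9.5% | 14.2% |

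If the removed patients have only the arm's average risk (r = 0.53), p stays at 0.53 and the error at 2.5%.

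**Check by Cox simulation** (4,000 runs per case, exponential times, 10% uniform drop-out, truth at the margin):

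| Would-be events lost before being recorded | Error if removed | Error if censored just before the event |
|---|---|---|
| None | 2.5% | 2.5% |
| 5% of abrupt-stop events (about 8 patients) | 4.7% | 6.0% |
| 10% of abrupt-stop events (about 15 patients) | 8.0% | 12.3% |
| 10% in both arms | 2.1% | not run |

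Censoring just before the event is an extreme case, but it shows that censoring instead of deletion does not remove the problem. The last row shows that inflation needs loss that differs between the arms.

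**The case against.** A reader might infer that section 7.4 removes the very patients who flare and take their own prednisone instead of the study tablets. The protocol does not support that. Starting unplanned systemic glucocorticoid is itself a primary event (section 5.1), also when the patient starts it, and section 7.4 says it will be assessed as part of the primary outcome. The primary-outcome interview takes place at the same day 7 contact as the first pill count. A patient whose event is recorded there has the endpoint and stays in both analysis sets. This objection stands, and it leaves a smaller group: patients excluded before any event is recorded.

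A reader might also infer that the investigator decides on the exclusion, or that the protocol has no outcome retrieval at all. Section 7.4 does not say who decides. Non-compliance could mean tablets or missed procedures, and section 8.4 can be read as a sign that poor tablet-takers were meant to stay. The lost-to-follow-up sentence in section 10.1.3 is worded generally, and section 11.5 permits inquiry with physicians. But the first sits among the rules for serious adverse events, the second obliges nobody, and neither names patients whom the trial has excluded. The undefined word is a reason to amend, since sites may apply it differently.

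Deletion from the analysis is not certain either; the patient may be censored. That stands, but censoring at exclusion is also informative if risk prompted the exclusion.

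Finally, the exclusion rates and risks are chosen, not documented, and the study team is blinded. This limits the size that can be claimed. Blinding does not make the loss equal, because the arms may differ in what leads patients to stop.

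**Conclusion.** The point holds in a limited form. Section 7.4 permits a post-randomisation exclusion on an undefined ground, no passage clearly secures the outcome of a patient so excluded, and the rule conflicts with section 8.4. An excluded patient without a recorded event may be left out of the ITT and PP sets or be censored at exclusion.

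The size is an illustration, not an estimate. With truth at the margin and loss confined to the abrupt-stop arm, the one-sided error rises from 2.5% to about 5% (3.9 to 6.3%) if 5% of that arm is removed at 80% (70 to 90%) event risk, and to about 9.5% (6.1 to 14.2%) if 10% is removed. Equal loss in both arms, or loss unrelated to risk, gives no inflation. The documents do not show that such loss has occurred or is expected. What they show is that the protocol permits it and that it is avoidable.

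**What to change.** Delete non-compliance as a reason for exclusion in section 7.4 and reconcile sections 7.4, 8.4, 8.5/9.2.5 and 11.4.1. State that:

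- non-adherence to the study tablets or missed procedures does not end participation in the trial;
- every randomised patient is followed to day 180 for the primary outcome, through the planned interviews or, if the patient cannot be reached, through the treating physician;
- these patients stay in the analysis, and compliance is recorded as data for section 8.4.

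Keep the existing rule in 8.5/9.2.5 that patients who withdraw are asked for permission to obtain the outcome from their physician. The change concerns data collection and analysis only; it alters no treatment and no sample size.

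The cost is a short amendment and some extra follow-up calls to less cooperative patients. The interviews themselves are already in the study schedule.

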### **11.5 Handling of missing data and drop-outs**

We will strive to make a complete case analysis, which will likely be feasible because the primary outcome is composed of clearly defined clinical events that can easily be tracked and inquired from the treating physicians if necessary. If a substantial proportion of patients have missing data, we will consider the use of multiple imputation.

Patients who leave the trial during the blinded treatment phase are replaced only if the number of total drop-outs is >10%.

---

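### Section 7.4 replaces drop-outs without condition and 11.5 only above 10%, although the 573 already carries a 10% allowance, so the number randomised is not fixed

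*Protocol*

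**What the plan says.** - **Section 7.4**, after noting that patients may withdraw in either the treatment or the follow-up phase: "Substitute patients for drop-outs will be recruited". It gives no threshold and refers the reader to 9.2.5, not to 11.5.
- **Section 11.5**: patients who leave during the blinded treatment phase "are replaced only if the number of total drop-outs is >10" percent.
- **Section 6.1**: "In total, 573 patients will be enrolled". The synopsis gives the same total.
- **Section 11.2**: "To achieve a power of 80%, 573 patients (95% CI, 565 to 580) need to be included". The assumptions behind this figure include 10% drop-out, spread uniformly over the six months.
- **Section 9.2.5** (same text in 8.5): patients who withdraw during treatment count as drop-outs, and nothing more is said about them. Those who withdraw during follow-up are asked to let their physician be contacted about the primary outcome, and are right-censored at last contact if they refuse. No replacement threshold appears here.
- **Section 11.4.1**: the ITT set holds only randomised patients whose primary endpoint is available, and the PP set holds the same patients. Section 11.4.2 runs the primary analysis on the PP set.

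**The concern.** A site following 7.4 recruits a substitute for each drop-out. A site following 11.5 recruits none until losses pass 10%. The protocol does not say which rule governs or, above 10%, whether all leavers or only the excess are replaced. Because the planned size already allows for 10% loss, replacing within that 10% exposes additional patients for a loss already paid for.

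A second question is what happens to the data of a patient who has been replaced. The first four weeks are when one arm is off glucocorticoid and the other is still tapering. If someone who leaves then is treated as having no available endpoint, a substitute could take that patient's place in the primary analysis. If leaving were related to symptoms or relapse, a noninferiority comparison could lose the very patients who matter most.

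**Working it through.** **Inputs, all from section 11.2.** The 6-month event rate: "the proportion of patients with an event, is 40%, both for the control and the experimental arms". The margin: "The non-inferiority margin is defined as an absolute increase of the event rate by 13% over 6 months". The decision rule: "upper limit of the two-sided 95% confidence interval of the hazard ratio lies below the critical hazard ratio". Power is 80%, allocation 1:1, and drop-out 10%, uniform over six months.

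**1. Reproduce 573 and locate the allowance.**
- Critical HR = ln(0.60 − 0.13) / ln(0.60) = 1.478, as stated.
- Events (Schoenfeld, two-sided 5%) = 4 × (1.960 + 0.842)² / (ln 1.478)² = 206.
- Patients without loss = 206 / 0.40 = 515.
- With 10% loss = 515 / 0.90, rounded up = 573.

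The protocol obtained 573 by simulation, not by this division. Simulating its stated set-up (exponential times, Cox model, 10% uniform drop-out, N = 573, 1,500 runs) gave power of 0.81 with about 219 events. On either route the 10% is inside the 573.

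**2. Enrolment at the planned 10% drop-out.** Expected drop-outs = 573 × 0.10 = 57.

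| Rule | Calculation | Enrolled |
|---|---|---|
| 11.5 (threshold not exceeded) | 573 | 573 |
| 7.4, treatment-phase leavers only, uniform loss | 57 × 28/180 = 9; 573 + 9 | about 582 |
| 7.4, all drop-outs, one substitute each | 573 + 57 | about 630 |
| 7.4, all drop-outs, until 573 complete | 573 / 0.90 | 637 |

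The excess is therefore 9 to 64 patients, depending on who counts as a drop-out and whether substitutes are themselves replaced.

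**3. What the double allowance buys.** With 573 fully followed patients, events = 573 × 0.40 = 229, and power = Φ(√(229/4) × ln 1.478 − 1.96) = 84%, against the planned 80%.

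**4. Does loss above 10% threaten power?** That depends on whether leavers contribute censored time. Under uniform loss, a fraction 1 − 0.40/0.511 = 0.217 of drop-outs have their event before leaving (0.511 = −ln 0.60). At 20% loss with N = 573, in an unstratified Cox model:
- Leavers censored at exit: 573 × (0.80 × 0.40 + 0.20 × 0.217) = 208 events, power 80.5%.
- Leavers contribute nothing: 573 × 0.80 × 0.40 = 183 events, power about 75%.

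**5. Ambiguity inside 11.5.** At 15% loss there are 573 × 0.15 = 86 drop-outs. Making good only the excess over 10% (restoring 516 completers) needs 516 / 0.85 = 608 enrolled. Replacing all of them, if all left in the treatment phase, needs about 659 (573 + 86) to 675 (573 / 0.85).

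**The case against.** **The two rules can be read together.** Section 7.4 may be the general statement and 11.5 the condition on it. This is a possible reading, but 7.4 does not cite 11.5, and the section it does cite has no threshold. The reader should not have to infer it.

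**The scope of 7.4 is narrower than it looks.** Section 9.2.5 applies the word drop-out to patients who leave during treatment and describes physician inquiry in follow-up as preventing drop-out. This stands. It means that 57 to 64 extra patients is the upper end of the range, with about 9 at the lower end.

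**Replacement biases the result.** A reader might infer that recruiting substitutes pushes the comparison toward no difference. The documents do not support that. Neither 7.4 nor 11.5 says that a replaced patient leaves the analysis, and adding patients does not by itself bias the hazard ratio or inflate type I error. Participants, physicians and study staff are blinded, and unplanned glucocorticoid treatment for relapse or symptoms is already a primary event. What remains is a gap: 9.2.5 provides neither inquiry nor censoring for treatment-phase leavers, and 11.4.1 requires an available endpoint. Section 10.1.3 provides physician inquiry for some leavers, in the context of serious adverse events, but not as a general rule.

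**The threshold in 11.5 must go because power never needs it.** A reader might also infer this, but step 4 shows that it holds only if leavers are censored and retained. A rule that acts beyond the built-in allowance does not double-count and is a legitimate design choice.

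**Conclusion.** The contradiction between 7.4 and 11.5 is real, and the protocol does not resolve it. At the planned 10% drop-out, 11.5 leaves enrolment at 573. Section 7.4 raises it to about 582, or to 630 to 637 on the widest reading, although the 573 already covers that loss. The lower figure assumes uniform loss over 180 days and a 28-day treatment phase. The upper figures assume that every drop-out is replaced.

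The effect on inference is conditional. It arises only if treatment-phase leavers are taken out of the ITT and PP sets, which the text permits but does not order. Neither the direction nor the size of any resulting bias can be calculated from the protocol. This is a minor point, worth correcting because it is cheap and because it settles how many patients are randomised and who is analysed.

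**What to change.** 1. **Sections 7.4 and 11.5:** give one rule in both places. State that 573 includes the 10% drop-out allowance and that replacement, if kept, covers only the excess over 10%. Dropping replacement altogether is an option, not a requirement.
2. **Sections 9.2.5 and 11.4.1** (and the duplicate text in 8.5): state that every randomised patient, replaced or not, stays in the primary time-to-event analysis, censored at last documented contact if no event is known.

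The cost is a set of small edits to 7.4, 9.2.5, 11.4.1 and 11.5. The second change alters the definition of the analysis sets, so 11.4.2 and the complete-case wording in 11.5 need to be read against it. The blinded re-estimation in 11.4.4 is a separate rule and can stay as it is.
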